#### Experimental Condition: EMIcompass Intervention Plus TAU

The EMIcompass intervention will be delivered by trained psychologists within a 6-week period in addition to TAU to individuals allocated to the experimental condition. TAU consists of all the treatment individuals received before inclusion in the study, including their general practitioner, psychiatrist, and clinical psychologist, except for treatment using elements of third-wave CBT. The manualized EMIcompass intervention consists of four biweekly sessions (three training sessions and one review session) with a duration of 45-60 minutes administered face-to-face or using a certified and encrypted video conferencing system and a 6-week compassion-focused EMI. An optional on-demand session will be offered if participants are unable to complete tasks between sessions or report acute psychological distress so that a scheduled session cannot be followed as per the manual. The EMI, which translates the training from the intervention sessions into individuals’ daily lives, will be administered through a smartphone-based app (movisensXS, movisens GmbH) running on dedicated study smartphones. The first three sessions are based on elements of compassion-focused therapy [68]. In line with our pilot study [53], compassion-focused therapy principles and techniques are introduced in these guided sessions. The first session aims to familiarize the participants with the app offering EMI. Further, practical tasks to activate the soothing system, as a key emotion regulation system in compassion-focused therapy, are presented and trained together with the psychologist, as described elsewhere [88]. Face-to-face sessions also offer the opportunity to reflect on the progress and problems participants face with EMI. In the last session, progress with all tasks will be reviewed and subjective improvement in, compliance and satisfaction, and acceptance of the EMIcompass intervention will be assessed.

The app will offer EMI tasks according to three types of delivery schemes: (1) enhancing, (2) consolidating, and (3) interactive EMI tasks that aim for ecological translation of therapeutic principles and techniques to daily life. Participants will be asked to complete one *enhancing task* per week, practicing new compassion-focused tasks such as self-compassionate writing, experiencing emotions as a wave, and discovering their own compassionate self. Furthermore, participants will be offered *consolidating tasks* covering components of *enhancing tasks* from previous days. The components of *consolidating tasks* will be extended each time an *enhancing task* has been presented until all components are covered. In addition, participants will be offered to complete a brief EMA of momentary stress, affective disturbance, and threat anticipation six times per day, 3 days per week. On the basis of these EMAs, *interactive* tasks will be offered if participants score high on momentary stress or negative affect. The threshold for triggering interactive tasks will be either high momentary negative affect operationalized as a score of 4 or higher (on a 7-point Likert scale ranging from 1-7) on items of established and validated EMA measures of negative affect (Textbox 2) or high momentary stress based on items of established and validated measures of EMA of event-related, activity-related, or social stress (ie, a score <0 on a bipolar scale ranging from −3 to 3).

Participants will be instructed in detail in the semantic meaning of the 7-point Likert and bipolar scales and encouraged to carefully observe moment-to-moment variation in, and make use of the full range when rating, these scales on EMA items that have been previously used and validated to measure moment-to-moment variation in stress or negative affect. Given that a crucial element of compassion-focused therapy is for individuals to use compassionate imagery in moments of high stress or negative affect, these interactive tasks reflect an important component of the EMIcompass intervention. Participants can decline the EMI tasks in each delivery scheme. After completing the intervention period, participants will return the study devices and will no longer have access to the app.

Ecological momentary assessment domains and measures.

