### Clinical Feasibility, Acceptability, Treatment Adherence, and Intervention Fidelity

Clinical feasibility will be assessed in relation to the trial methodology and the delivery of the EMIcompass intervention to youth with early mental health problems. The feasibility of the trial methodology will be assessed based on the following criteria: (1) successful recruitment of at least 96 participants during the study period; (2) assessment of inclusion criteria in 95% of potential participants after obtaining written consent; (3) successful randomization of at least 92 participants after completion of eligibility and baseline assessment; and (4) a retention rate of at least 85% for assessment of outcomes at least at one of the two time points at postintervention and 4-week follow-up. In addition, the following criteria will be used for establishing the feasibility of delivering the EMIcompass intervention, including its acceptability, intervention adherence, and intervention fidelity: (1) satisfaction with the EMIcompass intervention in general, ease of use, accessibility and comprehensiveness of various components of the intervention in a debriefing questionnaire [30,90], and the subjective quality of EMIcompass using the mobile application rating scale [91]; (2) compliance with, and adherence to, the EMIcompass intervention protocol based on a satisfactory level of session attendance, an adherence checklist covering all core components [29,30,92], and adherence to EMI tasks (ie, mean number of consolidating/interactive EMI tasks completed per week); and (3) fidelity to the EMIcompass intervention protocol based on independent ratings of a random selection of audio recordings of three face-to-face sessions, including fidelity to session protocol (ie, independent rating of core components delivered by trained psychologist), ability to model and embody the spirit of compassion, and the use of microskills in compassion-focused therapy assessed by the Compassion Focused Therapy-Therapist Competence Rating Scale [93].

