### Statistical Analysis

The primary objective of this exploratory RCT is to establish the feasibility of the trial methodology and intervention delivery and initial signals of efficacy on the candidate primary outcome (ie, psychological distress) as a basis for a future definitive trial. In addition, this trial seeks to obtain parameter estimates (95% CI) for the effects on primary and secondary candidate mechanisms and candidate secondary outcomes. A detailed Statistical Analysis Plan [113] has been agreed with the DMEC and the TSC and has been preregistered and published on the Open Science Framework. It was registered while collecting the data before study completion and accessing the locked database. Descriptive statistics will be used, and CIs will be constructed as appropriate to compute basic sample characteristics and address the primary aim of establishing the feasibility of the trial methodology and intervention delivery based on the criteria described above and in further detail in the Statistical Analysis Plan using three categories (in line with a traffic light system): (1) feasibility fully established (green), (2) feasibility established, but study procedures need to be modified (yellow), and (3) feasibility not established (red) [113]. The analysis of candidate mechanisms and initial signals of efficacy has been described in detail in the Statistical Analysis Plan [113] and will be an intention-to-treat analysis or an available case analysis following intention-to-treat principles, with data from all participants entered into the analysis, including those who have low adherence to or who will drop out from the intervention. We will make every effort to assess all participants at postintervention and 4-week follow-up. Linear mixed modeling in Stata 16 will be used to compare candidate mechanisms and outcomes between experimental and control conditions at postintervention and 4-week follow-up. The primary candidate outcome of psychological distress measured at postintervention and 4-week follow-up will be entered as the dependent variable and psychological distress measured at baseline, group status (3-level factor), time (2-level factor), and condition (2-level factor) as independent variables. The main effect of condition on psychological distress will be parameterized so that it reflects the difference between the two conditions at the two follow-up time points (ie, postintervention and 4-week follow-up), which will be tested (at α=.05) by a Wald-type test with df=1, which tests the joint null hypothesis of no difference at both follow-up time points against the alternative hypothesis that there is, on average, a difference across the two follow-up time points. In addition, given the exploratory nature of this trial, with the main goal of establishing feasibility and obtaining parameter estimates for a future definitive RCT, 95% CI for the two time-specific contrasts of a time×condition interaction term will be inspected to obtain estimates for the differences across conditions at each of the two time points, with a time × condition interaction and a baseline psychological distress×time interaction added as independent variables to the previous model. Within-subject clustering of repeated measures (postintervention and 4-week follow-up) will be taken into account by including a level-2 random intercept and allowing the models’ level-1 residuals to be correlated with a completely unstructured error variance-covariance matrix. The model will be fitted using restricted maximum likelihood estimation. The analysis of secondary candidate outcomes and primary and secondary candidate mechanisms will, in principle, follow the same steps, focusing on 95% CIs (rather than P values at α<.05). Multilevel moderated mediation analysis of EMA data will be used to explore whether the effects of condition on primary (ie, psychotic, manic, anxiety, or depressive) symptoms are mediated via stress reactivity, threat anticipation, negative affective appraisals, and interpersonal sensitivity [42]. As participants will be randomly assigned to experimental and control conditions, no differences across conditions are expected in other study parameters (sociodemographic characteristics, alcohol or substance use, and childhood trauma). No statistical tests will be performed on these study parameters at baseline.

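### Satisfaction, acceptance and subjective improvement have only one stated assessment time, the fourth session, so on the plan as written early leavers are not asked and acceptability may look too favourable

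*Protocol article*

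**What the plan says.** The section on the experimental condition describes the sessions: "The manualized EMIcompass intervention consists of four biweekly sessions (three training sessions and one review session"). It also says who gives them: "The EMIcompass intervention will be delivered by trained psychologists within a 6-week period". The timing of the acceptability measures comes at the end of the section's first paragraph, in the sentence on what is reviewed and measured: "In the last session, progress with all tasks will be reviewed and subjective improvement in, compliance and satisfaction, and acceptance of the EMIcompass intervention".

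The section on clinical feasibility, acceptability, adherence and fidelity makes these measures part of the first criterion for intervention delivery. It names two instruments. One covers "satisfaction with the EMIcompass intervention in general, ease of use, accessibility and comprehensiveness of various components of the intervention in a debriefing questionnaire"; the other rates "the subjective quality of EMIcompass using the mobile application rating scale". No time point, respondent set or administrator is given there for either. The second criterion in that section is separate: "compliance with, and adherence to, the EMIcompass intervention protocol based on a satisfactory level of session attendance", together with an adherence checklist and the number of EMI tasks completed.

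Under Statistical Analysis, feasibility is part of the primary objective and is graded green, yellow or red. The grading is set out further in the Statistical Analysis Plan, which is not shown.

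**The concern.** The only time given for asking about satisfaction and acceptance is the end of treatment. A participant who stops after the first or second session does not reach that point. Those who leave early may well include those who found the intervention least acceptable, and on the stated plan their views are not collected. The group starts out favourably disposed, since willingness to take part in the intervention is an inclusion criterion.

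The setting is a second, smaller worry. Ratings of a treatment given during a session of that treatment may be kinder than ratings given elsewhere.

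At stake is the feasibility judgement on which a definitive trial would be built. If the ratings come from completers alone, that trial could keep components that early leavers disliked without anyone having recorded it. An analysis plan can set thresholds and denominators, but it cannot recover answers that were never requested.

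**Working it through.** The article states no satisfaction target, no expected value and no expected share missing session 4, so there is no plan figure to reproduce. The check is a reading of the sections together, followed by a sensitivity range.

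**Reading the sections together**

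1. Timing: the experimental-condition section places the assessment in the last session. No other section gives another time.
2. Instruments: the feasibility section names them without a time, so it neither confirms nor widens the session-4 assessment.
3. Leavers: the attendance criterion counts how many stopped. It does not record what they thought or which components they disliked.
4. Position of session 4: four sessions two weeks apart fall at about weeks 0, 2, 4 and 6. Session 4 therefore lies close to the postintervention assessment, which is sought from all participants whatever their attendance.

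**Sensitivity range**

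Inputs:
- Arm size: 92 randomised at 50:50 gives 92/2 = 46 (Sample Size; Randomization and Blinding).
- Number missing session 4: m = 6, assumed. The article expects a loss of about 6 per condition, but that is loss from outcome assessment, not from sessions, so it serves only as a plausible order of size. Values of 2 and 12 are also shown.
- Proportion satisfied among attenders: 0.85, assumed.
- Proportion satisfied among those missing session 4: s, assumed, varied from 0.85 down to 0.

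Formulas:
- Arm-wide proportion = [(46 − m) × 0.85 + m × s] / 46.
- Overstatement by the attenders-only figure = (m/46) × (0.85 − s).

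With m = 6 (6/46 = 13.0%):

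| s | Arm-wide proportion | Overstatement (points) |
|---|---|---|
| 0.85 | (34.0 + 5.1)/46 = 0.850 | 0 |
| 0.60 | (34.0 + 3.6)/46 = 0.817 | 3.3 |
| 0.40 | (34.0 + 2.4)/46 = 0.791 | 5.9 |
| 0.20 | (34.0 + 1.2)/46 = 0.765 | 8.5 |
| 0 | (34.0 + 0)/46 = 0.739 | 11.1 |

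At the extreme s = 0, m = 2 gives (2/46) × 0.85 = 3.7 points and m = 12 gives (12/46) × 0.85 = 22.2 points. For every m the lower end is 0. Any effect of answering within a treatment session is not in these figures, and the article offers nothing from which to estimate it.

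**The case against.** The strongest reply is that the article reports what happens in the last session and does not say that early leavers go unasked. The questionnaire and the app rating scale are not tied to session 4 where they are named. How non-completers are handled is the kind of detail that a condensed article leaves to the full protocol or the analysis plan. This stands as a limit on certainty: an unstated route may exist. It does not remove the point, because the article does fix a time, and following it as written leaves leavers out.

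Three stronger readings are tempting and are not supported:

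- A reader might infer that the treating psychologist collects or sees the ratings. Psychologists deliver the sessions, but no administrator is named, and intervention-specific data such as clinical feasibility already go to a separate database.
- A reader might infer a contradiction with the intention-to-treat commitment, "including those who have low adherence to or who will drop out from the intervention". That phrase concerns the analysis of candidate mechanisms and initial efficacy signals. It makes no promise about ratings collected in one arm.
- A reader might infer that a false green rating is built in. The article gives no satisfaction cutoff, and poor attendance would show under its own criterion, so that cannot be demonstrated.

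It is also fair to say that someone who left after one session cannot rate components never received.

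**Conclusion.** The point holds in conditional form. The last session is the only stated time for satisfaction, acceptance and subjective improvement. On that plan, participants who stop earlier are not asked, and the acceptability criterion is likely to look too favourable if they are less satisfied. The direction rests on that assumption. The bias is zero if everyone attends session 4, if leavers are equally satisfied, or if leavers are asked by a route the article does not mention. It would therefore be wrong to call the measure biased upward as a matter of fact.

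With 6 of 46 missing session 4 and 85% of attenders satisfied, the overstatement is 0 to about 11 percentage points. Only the arm size comes from the document. The separate attendance criterion softens the consequence but does not supply the missing views. The point merits a change because the measure serves the primary objective and the remedy is small.

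**What to change.** In the experimental-condition and feasibility sections, state that the debriefing questionnaire, the app rating scale and the subjective-improvement items go as self-completed REDCap forms, at the postintervention time point, to all participants randomised to EMIcompass, regardless of sessions attended. They should not pass through the treating psychologist, nor through the blinded assessor, whose masking they would threaten. The separate database already planned for intervention-specific data can hold them. Report the number responding out of all randomised to that arm, and show results by completer status. The review of progress in the last session is unaffected.

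The cost is a few minutes of self-completion moved to an existing platform and time point. Some early leavers will not respond, and others can rate only what they received, but the non-response becomes visible. Enrollment was complete by May 2021, with last assessments due in August 2021. The change therefore reaches only remaining participants and any early leavers who can still be contacted. For everyone else, the denominator, the collection route and the split by completer status can still be reported.

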**Momentary stress**
Momentary stress was operationalized as unpleasant events, activities, and social situations in daily life. In line with previous research, we distinguished three different types of stress, that is, event-related stress, activity-related stress, and social stress [43,89]. Participants will be asked to report the most important event that happened in the time since the last assessment. This event will be subsequently rated on a 7-point Likert scale (−3=very unpleasant, 0=neutral, 3=very pleasant) comprising the event-related stress measure. Activity-related stress will be assessed by asking participants to report their current activity and then judge the valence of the activity (“This is...”) using a 7-point Likert scale (1=very unpleasant, 7=very pleasant). Further, social stress will be measured by asking participants to evaluate the social context when other people were present as well as when they were alone by answering the items “I am taking care of myself”/“I am taking care of somebody” and “I would rather be alone”/“I would prefer to have company” using two 7-point Likert scales and the item on social valence (“This is...” rated on the 7-point Likert scale from 1=very unpleasant to 7=very pleasant)
**Negative affect**
Six items will be used to assess negative affect (anxiousness, loneliness, insecurity, anger, annoyance, and feeling down), using 7-point Likert scales ranging from “not at all” (rating of 1) to “very much” (rating of 7)
**Negative affective appraisals**
In case participants report negative affect (ratings >3), two items on how they cope with their negative affect will be displayed: “I want to change my negative feelings” and “I would like to get rid of my negative feelings” using two 7-point Likert scales

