Compassion-focused interventions are third-wave cognitive behavioral therapy (CBT) approaches that use a wide range of innovative therapeutic techniques for enhancing emotional resilience by activating emotion regulation systems related to self-compassion, self-acceptance, and positive affect rather than those related to stress, threat, anxiety, and depression [68-70]. Indeed, there is meta-analytic evidence on compassion-focused interventions treating various conditions [71-73], such as depression and anxiety [74], psychosis [75], and general distress [76]. Compassion-focused interventions involve the use of techniques that seek to access emotion regulation processes through imagery rather than rational understanding [68,69]. In doing so, compassion-focused interventions aim to enhance emotional resilience by developing specific affective regulation patterns and, thereby, reduce reactivity to stress, hypervigilance for threat, interpersonal sensitivity, and negative affective appraisals. Experimental evidence indicates that compassion-focused intervention techniques can reduce negative affect and paranoia in moments of high stress [77,78]. Therefore, compassion-focused interventions are particularly promising for targeting these putative transdiagnostic mechanisms. Building on these pieces of evidence, we have recently developed a novel, accessible, transdiagnostic, compassion-focused, hybrid intervention to enhance resilience in youth with early mental health problems—the EMIcompass intervention [53], which consists of an EMI plus face-to-face training sessions. Although there is preliminary evidence on the feasibility and initial therapeutic effects of the EMIcompass intervention from an uncontrolled pilot study [53], robust evidence on the underlying mechanisms, feasibility, and initial signals of efficacy of EMIcompass from an exploratory trial is pending.

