#### Primary Candidate Mechanism

The primary candidate mechanism is a reduction in stress reactivity acquired by EMA from baseline to postintervention for the experimental condition compared with the control condition. EMA will include eight assessments per day, scheduled at random within set blocks of time, for 6 consecutive days at baseline, postintervention, and follow-up [43,95]. Momentary stress will be assessed using established and validated EMA measures of event-related stress, activity-related stress, and social stress (Textbox 2) [43,89]. We will compute a composite momentary stress measure (ie, the mean score of event-related, activity-related, and social stress) in line with the literature [52,96,97] and the EMIcompass pilot study [53]. Negative affect will be assessed using an established and validated EMA measure of negative affect [43]. Stress reactivity as the primary candidate mechanism will be computed in linear mixed models with composite momentary stress as the independent variable and negative affect as the outcome variable [43,89,95].

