#### Secondary Candidate Mechanisms

Secondary candidate mechanisms (Multimedia Appendix 1 and Textbox 2) measured using EMA include threat anticipation, negative affective appraisals, emotional resilience to stress (operationalized as attenuated recovery in positive affect in response to minor stressors), and elevated stress reactivity (ie, increased negative affect) in response to event-related, activity-related, and social stress using subscale scores of the EMA stress measure. Threat anticipation will be additionally assessed using the Threat Anticipation Measure [62], asking participants to estimate the future likelihood of a list of negative, neutral, and positive events happening to themselves and other people [61-63]. Interpersonal sensitivity will be assessed using the Interpersonal Sensitivity Measure [98] in addition to EMA. Resilience will be measured using the Connor-Davidson Resilience Scale [99] and the Resilience Scale [100]. Furthermore, the Self-Compassion Scale [101], the Fife Facet Mindfulness Questionnaire [102], and the Cognitive Emotion Regulation Questionnaire [103] will be used to assess self-compassion and emotion regulation. In addition, we will assess physiological markers of stress reactivity using a sensor for ambulatory ECG and actigraphy (movisens ECGmove4) during the 6-day EMA at baseline, postintervention, and at follow-up.

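### Appraisals are recorded only when negative affect exceeds 3, so their arm contrast and mediation path are conditional on a post-randomisation variable and should be labelled as such

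*Protocol article*

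**What the plan says.** The appraisal items are gated. Textbox 2, Negative affective appraisals: "In case participants report negative affect (ratings >3), two items on how they cope with their negative affect will be displayed". The gate is the momentary negative affect rating. Textbox 2, Negative affect: "Six items will be used to assess negative affect (anxiousness, loneliness, insecurity, anger, annoyance, and feeling down"), each rated 1 to 7. Whether one item above 3 suffices or the mean must exceed 3 is not said.

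The gate also operates after randomisation. Primary Candidate Mechanism: "EMA will include eight assessments per day, scheduled at random within set blocks of time, for 6 consecutive days at baseline, postintervention, and follow-up".

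Appraisals are listed among the secondary mechanisms "measured using EMA include threat anticipation, negative affective appraisals, emotional resilience to stress", and no ungated instrument is named for them. Objectives lists them both as a mechanism on which the intervention's effect is tested and as a possible mediator. Statistical Analysis sends secondary mechanisms, in principle, through the same mixed-model steps as the primary outcome, with emphasis on 95% CIs. It also asks whether condition effects on symptoms "are mediated via stress reactivity, threat anticipation, negative affective appraisals, and interpersonal sensitivity". None of these sections limits the target to moments of raised negative affect.

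Negative affect is something the intervention should change. Stress reactivity, the primary candidate mechanism, is modelled with "composite momentary stress as the independent variable and negative affect as the outcome variable". Background says that "compassion-focused intervention techniques can reduce negative affect and paranoia in moments of high stress".

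**The concern.** Whether an appraisal is observed depends on negative affect at that prompt. If EMIcompass lowers negative affect, fewer prompts open the gate in the experimental arm, and those that do come from a different selection of moments and people than in the control arm. Comparing the recorded appraisals then compares two subsets formed after randomisation by a variable that the intervention targets. Randomisation balances the arms as a whole, not these subsets. The mediation path through appraisals inherits the problem.

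At stake is what the trial can say about this mechanism. A difference, or its absence, would be read as the effect of EMIcompass on appraisals and could guide the choice of mechanisms for the definitive trial. It may partly reflect which prompts were displayed.

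**Working it through.** The document gives no figure for this point, and no distribution of negative affect or of its relation to appraisals. There is nothing to reproduce, and every parameter below is an assumption used to show a range.

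**1. Calculation by truncated normal.** Let negative affect be N(0,1) in the control arm and N(-0.3,1) in the experimental arm, with items displayed above a cut c. Let p0 be the control display rate, so c = Φ⁻¹(1 - p0). Appraisal is linear in negative affect and treatment acts on it only through negative affect.

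- Control mean among displayed prompts: φ(c)/p0.
- Experimental display rate: p1 = 1 - Φ(c + 0.3).
- Experimental mean among displayed prompts: -0.3 + φ(c + 0.3)/p1.

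For p0 = 0.30, c = 0.524. The control mean is 1.159, p1 = 0.205 and the experimental mean is 1.086. The displayed-prompt difference is 1.159 - 1.086 = 0.073, against 0.30 over all prompts: 0.073/0.30 = 24%.

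| Control prompts displayed | Share of all-prompt difference recovered |
|---|---|
| 20% | 20% |
| 30% | 24% |
| 40% | 29% |
| 60% | 39% |
| 80% | 54% |
| 90% | 67% |

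**2. The same model with a direct effect.** Take slope 0.4, a direct effect of 0.3 on appraisal and p0 = 0.30. All prompts: 0.4 × 0.3 + 0.3 = 0.42. Displayed prompts: 0.4 × 0.073 + 0.3 = 0.329. Recovered: 0.329/0.42 = 78%. With slope 0, only the direct effect remains and all of it is recovered.

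**3. Simulation with differences between persons.** 200,000 persons with 8 prompts each; person SD 0.9 and moment SD 1.0 for negative affect, rounded to 1-7; control mean 2.5 to 3.5; treatment lowers negative affect by 0.3 or 0.5 points. Results are simple differences of prompt means, not mixed-model estimates.

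- Prompts displayed, control v experimental: 23% v 13-17% at mean 2.5; 35% v 23-28% at 3.0; 50% v 35-41% at 3.5.
- No effect on appraisals, person-level correlation 0.5 between appraisals and negative affect: all-prompt difference about 0; displayed-prompt difference +0.04 to +0.10, against the intervention.
- Slope 0.4, person-level correlation 0.3 or 0.5: all-prompt difference -0.12 to -0.21; displayed-prompt difference -0.02 to +0.06.
- Appraisals unrelated to negative affect: the two agree within about 0.01.

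**4. Who still contributes.** A wave has 8 × 6 = 48 prompts. With the same variances and every prompt answered, about 76% to 99% of persons have at least one displayed prompt (lowest at control mean 2.5 with a fall of 0.5; highest at control mean 3.5 with no fall).

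**5. Check of a simple repair, scoring unshown items as 1.** Let appraisal average 5 when displayed and be untouched by treatment, with display falling from 30% to 20.5%. Control: 0.30 × 5 + 0.70 × 1 = 2.20. Experimental: 0.205 × 5 + 0.795 × 1 = 1.82. An apparent benefit of 0.38 points appears with no change in appraisal.

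**The case against.** The strongest defence is that the gate is partly the construct. The items ask about wanting to change or be rid of negative feelings, and they have little to refer to when such feelings are low. Appraisal given raised negative affect is a sensible target, and the plan nowhere claims an average over all prompts. This stands as a reason to keep a conditional estimand. It does not make the conditional contrast a randomised one, and the plan does not say that the target is conditional.

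A second defence is that Statistical Analysis refers to a separate analysis plan, not shown here, for detail. That plan may define the estimand or the handling of unshown items. It cannot supply answers to items that were never displayed.

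Third, stakes are limited: this is one of several secondary mechanisms in an exploratory trial, reported by CIs, with mediation described as exploration. Psychological distress and the primary stress-reactivity analysis are unaffected. This is so, and it sets the weight of the point.

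Two stronger readings are tempting. A reader might infer that the appraisal effect will be attenuated or reversed. The document does not support that: Background expects appraisals to fall in their own right, and the result runs from 20% recovery to full recovery depending on assumptions. The opposite signs in the simulation also come from assumed parameters. Low display rates are not established either: an any-item gate on six items, in a sample selected for emotional reactivity, could open often. A reader might also infer that those who improve most leave the analysis. Some may, but under the assumed variances most persons still contribute at least one prompt.

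**Conclusion.** The point holds as a limit on interpretation. Display depends on a variable measured after randomisation that the intervention is meant to lower, so neither the appraisal contrast nor the mediation through appraisals has the protection of randomisation. Bias follows if appraisals are related to negative affect at the level of the moment or the person. Its size and direction cannot be derived from the document. The illustrations run from about one fifth of the all-prompt difference recovered (no direct effect, 20% displayed) to all of it (no relation), and a small spurious difference is possible when there is no effect at all. The issue is worth correcting because it changes what may be claimed for this mechanism, but it does not touch the trial's main results.

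**What to change.** For this trial, where randomisation is complete and the display rule can no longer be changed:

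- State that the appraisal estimand is conditional on negative affect above 3, and whether that means any item or the mean.
- Report, by arm and wave, the proportion of answered prompts above 3 and the proportion of persons with at least one displayed prompt.
- Label the conditional arm contrast and the mediation through appraisals as descriptive, not as randomised effects.
- If an all-prompt estimate is wanted, fit a joint or two-part model of negative affect, which is observed at every answered prompt, and appraisal. Treat it as a sensitivity analysis that rests on its model. Do not score unshown items as 1: that turns a change in negative affect alone into an apparent appraisal benefit.

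For the definitive trial, consider showing the two items at every prompt.

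The cost is a little more analysis and a weaker claim for one secondary mechanism. Showing the items always would lengthen prompts slightly and would ask about negative feelings when few are present.
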